## Abstract

**Background:**

The lack of adequate randomized clinical trials (RCT) has hindered identification of new therapies that are safe and effective for patients with primary focal segmental glomerulosclerosis (FSGS), especially in patients who fail to respond to corticosteroids and immunosuppressive therapies. Recent basic science advances have led to development of alternative treatments that specifically target aberrant pathways of fibrosis which are relevant to disease progression in FSGS. There is a need for a flexible Phase II study design which will test such novel antifibrotic strategies in order to identify agents suitable for phase III testing.

**Methods/Design:**

The Novel Therapies for Resistant Focal Segmental Glomerulosclerosis (FONT) project is a multicenter Phase I/II RCT designed to investigate the potential efficacy of novel therapies for resistant FSGS. Adalimumab and galactose will be evaluated against conservative therapy consisting of the combination of lisinopril, losartan and atorvastatin. The sample size is defined to assure that if one of the treatments has a superior response rate compared to that of the other treatments, it will be selected with high probability for further evaluation. Comparison of primary and secondary endpoints in each study arm will enable a choice to be made of which treatments are worthy of further study in future Phase III RCT.

**Discussion:**

This report highlights the key features of the FONT II RCT including the two-step outcome analysis that will expedite achievement of the study objectives. The proposed phase II study design will help to identify promising agents for further testing while excluding ineffective agents. This staged approach can help to prevent large expenditures on unworthy therapeutic agents in the management of serious but rare kidney diseases

**Trial Registration:**

ClinicalTrials.gov, NCT00814255

## Background

The goal of therapy in proteinuric diseases such as primary FSGS is complete remission of proteinuria and preservation of renal function. However, this is rarely achieved in patients with FSGS that is resistant to standard treatment [1,2]. When corticosteroids and immunosuppressive therapy fail to induce remission in patients with primary FSGS, a number of agents are used as renoprotective therapy to delay progression of chronic kidney disease (CKD) to end stage kidney disease (ESKD). Angiotensin converting enzyme inhibitor (ACEi) and angiotensin II receptor blocker (ARB) are two such therapies that reduce proteinuria when used alone, with an additive effect when prescribed in combination [3-12]. Prescription of 3-hydroxy-3-methyl-glutaryl coenzyme A (HMG-CoA) reductase inhibitors in doses designed to treat dyslipidemia is also associated with stabilization of glomerular filtration rate (GFR) and improved kidney function in chronic non-diabetic nephropathies [13]. Combined use of an ACEi, an ARB, and an HMG-CoA reductase inhibitors represents optimal conservative medical therapy in patients with resistant FSGS and has been advocated as a standard renoprotective regimen [14-17].

Great strides have been made in understanding renal fibrosis. Tumor necrosis factor-α (TNF-α) is an inflammatory cytokine produced by a wide range of cells including macrophages and renal tubular epithelial cells. Several mechanisms for TNF-α-induced proteinuria in FSGS have been proposed including recruitment of leukocytes to the site of glomerular injury, induction of cytokines and growth factors, generation of oxygen radicals with increased glomerular endothelial cell permeability, cytotoxicity, and induction of apoptosis [18-21]. The potential for TNF-α antagonism to reduce proteinuria in resistant FSGS is based on the finding of elevated TNF-α levels in experimental models of the disease and in patients with FSGS, induction of proteinuria in animals by TNF-α from mononuclear cells taken from patients with FSGS, and reduction in proteinuria with a TNF-α antagonist in the angiotensin II-induced renal injury model and other models that resemble FSGS [22].

Published reports indicate that serum samples of nearly 50% of patients with primary steroid resistant FSGS have the capacity to increase the permeability of glomeruli to albumin, (P_alb_) during *in vitro *incubation and testing [23]. Standard conditions for these studies include incubation of glomeruli from normal rats with medium containing 2% vol/vol patient serum. A value of to ≥ 0.5 is defined as a positive test [24]. Addition of 10^-12 ^M galactose to the incubation medium containing patient serum completely prevents the increase in permeability. Removal of galactose by extensive dialysis of the medium restores P_alb _activity. Intravenous administration of galactose or chronic ingestion of galactose prior to obtaining serum markedly decreases P_alb _activity. Dialysis of sera obtained after galactose administration does not restore activity, suggesting that galactose enhances removal of a circulating permeability factor [25]. Savin and colleagues have postulated that increased hepatic clearance by galactose-binding proteins (galectins) may be responsible for removal of the permeability factor. There are case reports describing individual patients with FSGS who were given oral galactose for over 6 months and who demonstrated reduction in P_alb_, lowering of proteinuria, and stabilization of kidney function [26]. These findings raise the possibility that extended administration of galactose to lower P_alb _in patients with resistant FSGS may reduce proteinuria and delay progressive decline in kidney function [27].

The FONT trial (DK70341) is a combined Phase I/II project with an overall objective to identify promising new antifibrotic agents for further testing and distinguishing them from agents which are likely to be ineffective. A staged approach to drug evaluation is incorporated into the Phase II trial design to avoid large expenditures on unworthy and untested therapeutic agents for this serious disease.

## Methods/Design

### Study Design: General considerations

FONT II is a Phase II open-label RCT to choose which treatment or treatments are worthy of further study in future Phase III studies.

### Specific Aims

1. To evaluate two novel therapies for resistant FSGS - adalimumab, a human anti-TNF-α antibody, and galactose - compared to standard conservative therapy;

2. To identify one or more novel agents as candidates for evaluation in a future Phase III RCT; and

3. To create and sustain an infrastructure for the timely completion of RCTs in patients with rare glomerular diseases like primary FSGS.

### Primary and Secondary Outcomes

There will be a composite endpoint in which a patient will be classified as having a positive response if both of the following criteria are satisfied:

• Reduction in proteinuria (expressed as the protein:creatinine ratio in a first morning urine specimen) at 6 months by ≥ 50% of the value at the time of screening, AND

• Estimated GFR (eGFR) at 6 months ≥ 75% of the value at the time of randomization in those with an initial eGFR <75 mL/min/1.73 m^2 ^OR eGFR persistently ≥75 mL/min/1.73 m^2 ^in those whose renal function was ≥75 mL/min/1.73 m^2 ^at the time of randomization.

The proteinuria at the time of screening will be used to determine eligibility and efficacy. While an eGFR ≥40 mL/min/1.73 m^2 ^at screening will be used to determine eligibility, the eGFR at the time of randomization will be used to determine efficacy to account for the hemodynamic impact of intensified combination therapy with ACEi and ARB agents during the Run-In Phase (see below).

The proteinuria endpoint is an objective variable that can be quantitated in a bias-free manner. Although controversy remains over the potential use of proteinuria as a surrogate end point in definitive Phase III clinical trials, proteinuria is an ideal marker for use as an intermediate outcome in earlier phase trials. In particular, proteinuria responds to many therapies within several months, providing an outcome whose response can be assessed in relatively short-term studies [28]. The proteinuria component of the composite was formulated to require a large change (≥50% reduction) to increase the likelihood that changes classified as a positive outcome are clinically relevant and to reduce the influence of small perturbations as might be induced by minor hemodynamic changes. However, due to concerns that reductions in proteinuria may be the result of steadily declining kidney function rather than improvement in glomerular permselectivity, stabilization of eGFR is included in a composite primary endpoint. eGFR will be calculated using the Schwartz equation in patients ≤18 years of age at screening or the Cockroft Gault equation adjusted for body surface area in patients older than 18 years of age, in accord with procedures adopted in the FONT Phase I studies [29-31].

The composite primary outcome will be assessed in all patients enrolled in the trial and who are randomized to one of the three study treatments. In a subgroup analysis, the primary endpoint will be evaluated in the patients in the three experimental groups whose Palb at the time of enrollment exceeds 0.5.

### Secondary Endpoints

Key secondary renal endpoints will include the percent change in the first morning urine protein creatinine ratio from baseline to 6 months, the change in eGFR from baseline to 6 months, both evaluated as continuous variables, and time to a 50% reduction in eGFR and/or ESKD. Patient status [32], and quality of life will be assessed by age-appropriate QOL surveys and the Patient-Reported Outcomes Measurement Information System (PROMIS) score. The adverse effect profile will be determined by clinical evaluation and standard laboratory testing.

### Study Population

Inclusion and exclusion criteria for enrollment are defined in Table 1. The eligibility criterion for steroid resistance or intolerance is defined in recognition of a reluctance of nephrologists to routinely administer a prescribed course of corticosteroids to all patients because of the potential for serious adverse events. FSGS can occur as a consequence of genetic mutations in structural proteins in the podocyte [33-36]. Thus, confirmation of a disease-causing mutation in a podocyte protein is an eligibility criterion for the FONT II trial in patients who lack biopsy-confirmation of the diagnosis of FSGS. Although there is a lack of data on expected response rates to antifibrotic therapy in the presence or absence of podocyte mutations, progressive renal fibrosis is an intrinsic feature of primary FSGS, regardless of whether or not there is a defined genetic mutation. In any event, DNA specimens for storage in the NIDDK Biorepository will be obtained from all patients who enroll in the trial and consent to the procedure. There is no exclusion criterion based on obesity because antifibrotic agents should also be beneficial in patients with obesity-related FSGS.

**Table 1 T1:** FONT II Study Eligibility Criteria

Inclusion Criteria
1. Primary FSGS confirmed by renal biopsy

2. Failure to respond to prior therapy with at least one of the following immunosuppressive medications -- cyclosporine, tacrolimus, mycophenolate mofetil, sirolimus - or other agents prescribed to lower proteinuria

3. Age 1-50 years at onset of proteinuria

4. Age 1-51 years at time of randomization

5. Estimated GFR ≥40 mL/min/1.73 m^2 ^using Schwartz (age <18 yr) or Cockcroft-Gault (age ≥ 18 yr) formula at screening and ≥30 mL/min/1.73 m^2 ^at the end of the Run-In Period and prior to randomization

6. Up/c > 1.0 g protein/g creatinine on first morning void

7. Steroid resistance defined as failure to achieve sustained Up/c < 1.0 following a standard course of prednisone/prednisolone/methylprednisolone prescribed for FSGS therapy, OR contraindication/anticipated intolerance to steroid therapy defined as severe obesity, documented decreased bone density, family history of diabetes, or a psychiatric disorder.

8. Willingness to follow the protocol, including medications, baseline and follow-up visits, and procedures.

**Exclusion Criteria**

1. Lactation, pregnancy, or refusal of birth control in women of child-bearing potential

2. Participation in another therapeutic trial involving protocol mandated administration of a immunosuppressive medication concurrently or 30 days prior to randomization

3. Active/serious infection (including, but not limited to Hepatitis B or C, HIV)

4. History of malignancy

5. Abnormality in age appropriate cancer screening in accord with ACS 2003 guidelines

6. Patients with uncontrolled blood pressure > 140/90 or > 95th percentile for age/height at the end of the run in period

7. Diabetes mellitus, type 1 or 2

8. Organ or bone marrow transplantation

9. Congestive heart failure

10. History of myocardial infarction

11. SLE or multiple sclerosis

12. Hepatic disease defined as serum ALT/AST more than 2.5× the upper limit of normal

13. Hematocrit <27 vol%

14. Immunosuppressive therapy with cyclosporine, tacrolimus, mycophenolate mofetil, azathioprine, rapamycin, or cyclophosphamide in the 30 days prior or Rituximab in the 90 days prior to randomization

15. Use of corticosteroids in the last 30 days except for minimal dosage required for stabilization of edema

16. Prior treatment with the study medications, galactose or adalimumab

17. Allergy to one of the study medications, i.e., adalimumab, galactose, lisinopril, losartan, atorvastatin

18. Abnormal Pap smear (more than carcinoma in situ 1) unless treated and follow-up indicates a normal Pap smear

### Screening and Run In Phase

In order to achieve a comparable baseline assessment of proteinuria and GFR prior to initiation of one of the novel therapies, the patients will be taken off all immunosuppressive medications including corticosteroids (except for a minimal daily or alternate-day dosage to control edema if clinically indicated) for 30 days. In addition, patients will be placed on the maximal tolerated doses of lisinopril, losartan or atorvastatin, based on measurements of blood pressure, serum potassium, creatinine, and cholesterol concentrations. Patients must be on stable doses of the ACEi/ARB treatment for a minimum of 2 weeks prior to randomization into the FONT Phase II study to insure that the initiation of novel therapy does not coincide with a hemodynamically induced change in proteinuria. In order to fully implement the conservative medical therapy regimen in a timely manner, a maximum 12 week Screening/Run-In period will precede randomization (Figure 1).

**Figure 1 F1:**
[figure not shown]
**FONT II Trial Design**.

### Study Medications

Standard conservative medical therapy: All patients will receive a combination of the following three agents: 1) lisinopril: 2) losartan; and 3) atorvastatin. The maximum doses for patients weighing <40 kg will be: lisinopril 10 mg, losartan 25 mg, and atorvastatin 10 mg. For patients weighing >40 kg, the maximal doses will be: lisinopril 20 mg, losartan 50 mg, and atorvastatin 20 mg. Stable dosages of the ACEi and ARB must be achieved by the end of the Screening/Run-in period (2-12 weeks) and remain unchanged for the duration of the 6 month treatment period barring any clinical or laboratory side effects.

The following novel therapies will be administered for 6 months before assessing efficacy;

Adalimumab (Humira^®^): *TNF-α antibody*: The therapeutic dose of adalimumab will be 24 mg/m^2 ^(maximum dose: 40 mg) every other week as a subcutaneous injection for the entire treatment period. Although the pharmacokinetics (PK) data from the FONT Phase I Study indicated enhanced clearance of adalimumab in patients with FSGS and nephrotic-range proteinuria, the dose will not be increased above the standard amount in order to minimize the risk of adverse events [30,31].

Galactose: *sugar*: Galactose (Ferro Pfanstiehl, Waukegan, IL), 0.2 g/kg per dose (maximum dose: 15 g) will be administered orally twice a day. The sugar will be dissolved in 15-30 ml of water and the liquid will be ingested 15-30 minutes before breakfast and dinner.

### Study Protocol

Figure 1 outlines the course of the Phase II trial after completion of the Screening/Baseline period and receipt of study drugs at week 0. Patients will be evaluated after 2, 8, 16, and 26 weeks of the assigned experimental treatment. A follow-up evaluation will be performed at 1 month, 3 months, and 6 months after discontinuation of the novel therapy, and then every 6 months until the end of the funding period.

### Study Mandated Stop Points

• > 50% decline from baseline eGFR and <60 mL/min/1.73 m^2 ^OR a final level <20 mL/min/1.73 m^2^

• ESKD, i.e., initiation of dialysis or receipt of a renal transplant

• Serious Adverse Event (SAE), i.e. grade 4 Common Toxicity Criteria (CTC) toxicity

• Increase in ALT/AST to >2.5× the upper limit of normal

• Onset of congestive heart failure or a myocardial infarction

• Clinical onset of SLE and/or positive ANA ≥1:160

• Serious infection/sepsis

• Malignancy

• Pregnancy

### Statistical Considerations, Efficacy and Power

A hybrid Phase II design as described by Liu et al [37] will be used which incorporates a ranking/selection comparison [38,39] between the treatment groups as well as a minimum activity requirement within each treatment group. FONT II will include a sample size of 42 patients in each of the three treatment arms, with a total sample size of 126 patients. Up to 53 patients may be enrolled in the galactose arm (137 total subjects) to ensure a subgroup of 42 with a P_alb _> 0.5. Although the galactose arm was added after initiation of the study, patient enrollment was very low prior to this change. Therefore, introduction of galactose and removal of rosiglitazone are not anticipated to influence the study population. We next describe the assessment of the minimum activity requirement and the ranking/selection components of the study.

Minimum efficacy component: A two-stage procedure will be conducted to determine if the individual novel experimental treatments achieve a minimal level of efficacy that would signify that the therapies are sufficiently promising to warrant further investigation. In the first stage, patients will be enrolled until each of the 3 treatment groups has accumulated 17 randomized subjects. At this point, randomization will be temporarily halted, and there will be a 6 month pause during which the first set of patients assigned to each of the 3 arms will be allowed to complete the treatment period and have their response to the therapy evaluated. If in either of the experimental groups - adalimumab or galactose groups-- there are one or fewer responders among the first 17 randomized patients, that group will be dropped from further consideration. After the 6-month pause, the study will resume randomization until 42 patients (up to 53 patients may be enrolled in the galactose arm to ensure a subgroup of 42 with a P_alb _> 0.5) are accrued for each agent that passed the initial efficacy threshold.

This component of the design is based on the parameters p0, the estimated response rate to an "ineffective novel therapy", and p1, the projected response rate to an "effective novel therapy" that we would like to evaluate in a RCT. Based on experience gathered from the Glomerular Disease Collaborative Network (University of North Carolina, Chapel Hill, NC), we anticipate that optimal conservative medical therapy will result in response rate (≥50% reduction in proteinuria) of approximately 10%. Taking p0 = 10% and p1 = 30% (designating a 20% improved response for a successful novel therapy), the two-stage procedure described above has Type I and Type II error rates of 2% and 10%, respectively. Any treatment with at least 9 responses (out of 42 patients) will be identified as having a response rate sufficiently greater than 10% and considered to be an "active" agent worthy of further study in subsequent Phase III RCT.

The requirement of 2 or more responses for the two experimental treatments in the first stage reduces the risk of continuing to enroll patients into a treatment group for which the early results indicate a low response rate. On the other hand, the 2-stage design has at least a 98% probability of proceeding to the second stage if the true response rate of either of the two initial experimental treatments is 30% or greater. The overall type I and II error rates of 2 and 10% indicate that for each treatment group, the proposed design has a probability of 2% of incorrectly designating a regimen with a 10% response rate as "active", and a probability of 90% of correctly designating a regimen with a 30% response rate as "active".

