### Subgroup Analysis

It is anticipated that approximately 80% of the enrolled patients will have P_alb _> 0.5. This value represents the lower limit for increased levels of the permeability factor, which is the putative target of galactose treatment. Therefore, a secondary analysis will be performed in which the response rate of the Galactose arm will be computed separately for the subgroup with P_alb _> 0.5. The ranking-selection comparison of all three groups will also be repeated in patients with P_alb _> 0.5.

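### The rule of 9 responders out of 42 does not fit a galactose arm of up to 53 patients: the plan does not say which patients are counted, and the readings have different error rates

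*Protocol article*

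**What the plan says.** All references are to the Protocol article.

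- **Stage 1** (Statistical Considerations, Efficacy and Power). After 17 patients per arm, if in an experimental arm "there are one or fewer responders among the first 17 randomized patients, that group will be dropped from further consideration". P_alb plays no part in this rule.
- **Final rule** (same section). "Any treatment with at least 9 responses (out of 42 patients) will be identified as having a response rate sufficiently greater than 10" per cent. The 42 are not tied to P_alb.
- **Design parameters** (same section). "Taking p0 = 10% and p1 = 30% (designating a 20% improved response for a successful novel therapy"), the procedure "has Type I and Type II error rates of 2% and 10%, respectively". The chance of reaching stage 2 is put at 98% or more when the true rate is at least 30%.
- **Arm size** (same section, repeated under Ranking Selection Component). "Up to 53 patients may be enrolled in the galactose arm (137 total subjects) to ensure a subgroup of 42 with a P"_alb above 0.5.
- **Population** (Primary and Secondary Outcomes). "The composite primary outcome will be assessed in all patients enrolled in the trial and who are randomized to one of the three study treatments".
- **Role of P_alb** (Subgroup Analysis). About 80% of patients are expected to exceed 0.5. Of that cut-off the plan says: "This value represents the lower limit for increased levels of the permeability factor, which is the putative target of galactose treatment". In this subgroup the galactose response rate is estimated as a secondary analysis and the three-arm ranking is repeated. No threshold for calling galactose active is attached to the subgroup.

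**The concern.** The 9-of-42 rule and its error rates were worked out for an arm of exactly 42. At the plan's own 80% prevalence, 42 patients with P_alb > 0.5 require 42 / 0.8 = 52.5 enrolled, so the galactose arm is expected to reach about 53. The plan then has 53 patients in the primary outcome, 42 in the activity rule, and a further 42 defined by P_alb, and it does not say which of these the 9 responders come from.

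The rule decides whether galactose is put forward for Phase III. Under one reading an ineffective galactose regimen passes more than three times as often as stated. Under another, an effect of the size the trial looks for, in the patients for whom the arm was enlarged, is missed about twice as often as the stated 10%.

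**Working it through.** **Inputs from the protocol article.** p0 = 10% and p1 = 30%; stage 1 of 17 patients, continue with 2 or more responders; active with 9 or more of 42; galactose arm up to 53; 80% with P_alb > 0.5.

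**Assumption (ours).** When the effect is confined to the target, patients with P_alb ≤ 0.5 respond at 10%, the rate expected under conservative therapy. The range 0% to 20% is shown below.

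**Formula.** For n patients in total, final cut-off r and response rate p:

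A(n, r, p) = Σ over x = 2 to 17 of P[Bin(17, p) = x] × P[Bin(n − 17, p) ≥ r − x]

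Continuation past stage 1 is P[Bin(17, p) ≥ 2].

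**Step 1: the plan's own figures.**
- Type I error: A(42, 9, 0.10) = 2.03% (stated 2%).
- Power: A(42, 9, 0.30) = 91.1% (stated 90%).
- Continuation at 30%: 98.07% (stated at least 98%).

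All three reproduce.

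**Step 2: whole-arm rate if the effect is confined to the target.** 0.8 × 30% + 0.2 × 10% = 26%.

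**Step 3: whole-arm readings of the final rule.**

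| Galactose patients counted | Cut-off | Type I error at 10% | Power at uniform 30% | Power at 26% |
|---|---|---|---|---|
| 42 unselected | 9 | 2.03% | 91.1% | 78.8% |
| All 53 | 9 | 7.0% | 97.3% | 92.6% |
| All 53 | 10 | 3.3% | 96.2% | 88.9% |
| All 53 | 11 | 1.4% | 93.9% | 83.0% |

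Counting 42 unselected patients leaves 53 − 42 = 11 enrolled patients outside the decision.

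**Step 4: stage 1 on the first 17 randomized, final rule on 42 patients with P_alb > 0.5.** Of the first 17, k ~ Bin(17, 0.8) have the target. Let x ~ Bin(k, response rate with target) and y ~ Bin(17 − k, response rate without). Continue if x + y ≥ 2, and call active if x + Bin(42 − k, response rate with target) ≥ 9. Summing exactly over k, x and y:
- 10% in both groups: type I error 1.9%.
- 30% with target, 10% without: continuation 95.8%, power 89.3%.

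**Step 5: sensitivity of the 42-unselected reading to the assumption, at 80% prevalence.**
- 0% response without target: whole-arm rate 24%, continuation 94.0%, power 69.5%.
- 20% response without target: whole-arm rate 28%, continuation 97.1%, power 86.0%.

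**Step 6: stage 1 by itself.** The chance of dropping the arm is 1.9% at 30% and 4.2% at 26%.

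**The case against.** **The 90% and 98% are not wrong.** A reader might infer that they fail for galactose. The plan states both for a regimen whose own response rate is 30%, and both reproduce. It nowhere says that 30% is the rate among patients with P_alb > 0.5. Any design loses power below its p1. This objection stands, and the 78.8% describes a scenario rather than an arithmetic error.

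**The subgroup is not unused.** A reader might also infer that the extra patients serve no decision. The Subgroup Analysis section repeats the three-arm ranking in patients with P_alb > 0.5. With 42 galactose patients at 40% and about 34 (0.8 × 42 = 33.6) in each other arm at 25%, the exact chance of correct selection is about 86%, in line with the stated 85%. This also stands. What the subgroup lacks is an activity threshold.

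**Deciding on all randomized patients is a declared choice.** That is legitimate, and the effect may not be confined to the target, which the plan itself calls putative. But the choice then needs a cut-off for the number enrolled, and 9 over 53 does not keep 2%.

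**Stage 1 need not move.** It is tempting to restrict the first look to patients with P_alb > 0.5. At 80% prevalence that lowers the drop probability only from 4.2% to 1.9%. It needs about 17 / 0.8 ≈ 21 galactose patients before a pause that is tied to 17 in every arm. This is a trade-off, not a defect.

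**A lower prevalence proves little here.** The Background reports permeability activity in nearly 50% of patients with steroid-resistant disease. At 50% the whole-arm rate would be 20% and 9-of-42 power 45.8%. That figure comes from published samples, not from the plan's enrolment assumption, so no weight is put on it.

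**The population could be settled elsewhere.** Counting 42 unselected patients is not explicit for galactose, and the full protocol may settle it. Even so, the article prints the cut-off, the error rates and the larger arm together, and they do not agree unless the population counted is specified.

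**Conclusion.** The point holds as a mismatch between a decision threshold and the arm to which it applies. Counting 9 responders over 53 galactose patients raises the false-positive rate from 2% to 7.0%; this needs no assumption beyond p0 = 10% and the enrolment cap. Counting 42 unselected patients keeps 2% but sets aside up to 11 patients. It also has 78.8% power if the effect is confined to P_alb > 0.5 at 80% prevalence, with a range of 69.5% to 86.0% as response without the target varies from 0% to 20%. Applying the rule to 42 patients with P_alb > 0.5 comes close to the stated properties (1.9% and 89.3%), but the plan does not say this.

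The point does not show that the stated 90%, 98% or 85% are miscalculated, nor that the adalimumab rules need changing. It should be settled before the final galactose decision is made.

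**What to change.** **Preferred.** State that for galactose the final rule is at least 9 responders among the first 42 galactose patients with P_alb > 0.5 at enrolment. Keep the stage-1 rule on the first 17 randomized, and report the response rate in all galactose patients alongside. This uses a measurement and an enrolment cap already in the plan. The cost is that a claim of activity for galactose is limited to patients with P_alb > 0.5.

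The wording should also say what applies if 53 are enrolled and fewer than 42 qualify. At 80% prevalence P[Bin(53, 0.8) ≥ 42] = 63.3%, so a shortfall is quite possible, and the 89.3% assumes that 42 are reached.

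**Alternative.** If the sponsor prefers to decide on the whole galactose arm, state a cut-off recomputed for the number actually enrolled. At 53 patients, 11 responders keep the false-positive rate at or below 2% (1.4%), with power 93.9% at a uniform 30% and 83.0% if the effect is confined to P_alb > 0.5 at 80% prevalence. The cost is a higher cut-off and less power for a target-confined effect.

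Under either option, say that the 90% and 98% refer to a regimen with a true 30% response rate in the patients counted.

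### The go threshold of 9 responders and its 2% error rate are set for 42 patients; no threshold is given for a galactose arm of 43 to 53

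*Protocol article*

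**What the plan says.** All of the design text is in the protocol article, mainly under Statistical Considerations, Efficacy and Power.

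- **Planned size:** "FONT II will include a sample size of 42 patients in each of the three treatment arms, with a total sample size of 126 patients".
- **Exception for one arm:** "Up to 53 patients may be enrolled in the galactose arm (137 total subjects"). The stated reason is to obtain 42 galactose patients with P_alb above 0.5. The allowance is repeated in the description of the second stage of the minimum-efficacy procedure and again under Ranking Selection Component.
- **Stage 1:** if in an experimental arm "there are one or fewer responders among the first 17 randomized patients, that group will be dropped from further consideration".
- **Final rule:** "Any treatment with at least 9 responses (out of 42 patients) will be identified as having a response rate sufficiently greater than 10" per cent.
- **Assumptions:** "Taking p0 = 10% and p1 = 30% (designating a 20% improved response for a successful novel therapy").
- **Claimed properties:** "the two-stage procedure described above has Type I and Type II error rates of 2% and 10%, respectively". The next paragraph extends the claim to all arms: "for each treatment group, the proposed design has a probability of 2% of incorrectly designating a regimen with a 10% response rate" as active.

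Two other places bear on which patients the rule uses. Primary and Secondary Outcomes assesses the composite endpoint in all randomised patients. Subgroup Analysis makes the response rate among galactose patients with P_alb above 0.5 a secondary analysis.

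**The concern.** A fixed responder count means different things at different arm sizes. Nine of 42 is 21.4% and nine of 53 is 17.0%. The plan enlarges one arm but states a single count and a single pair of error rates for every arm.

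This component exists to keep inactive agents out of Phase III. If the count stays at 9 while the galactose arm grows, galactose faces a lower hurdle than adalimumab, and its chance of being called active when it is not exceeds the stated 2%. If instead only 42 galactose patients are meant, the text does not say which 42, and different choices can lead to different decisions from the same data.

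**Working it through.** **Inputs, all from the protocol article.** Stage 1 has 17 patients, and the arm continues with 2 or more responders. The arm is active with 9 or more responders in total. The null rate is p0 = 0.10 and the target rate is p1 = 0.30. Final arm size is n = 42, or up to 53 for galactose.

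**Formula.** With X1 the number of responders among the first 17, and r the final threshold:

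P(active) = Σ over x1 = 2,…,17 of P[Bin(17, p) = x1] × P[Bin(n − 17, p) ≥ r − x1]

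**Step 1. Reproduce the plan's figures (n = 42, r = 9).** The second stage has 42 − 17 = 25 patients. Type I error is 2.03%. Power at 30% is 91.1%, so type II error is 8.9%. The probability of passing stage 1 at 30% is 98.1%. The plan states 2%, 10% and at least 98%. Its calculation is sound for 42 patients, and the same method can be used for other sizes.

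**Step 2. Hold r = 9 and enlarge the arm.** At n = 53 the second stage has 36 patients. The terms at p = 0.10 are:

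| x1 | P(X1 = x1) | P(enough in 25) | Term, n = 42 | P(enough in 36) | Term, n = 53 |
|---|---|---|---|---|---|
| 2 | 0.2800 | 0.0095 | 0.0027 | 0.0628 | 0.0176 |
| 3 | 0.1556 | 0.0334 | 0.0052 | 0.1454 | 0.0226 |
| 4 | 0.0605 | 0.0980 | 0.0059 | 0.2892 | 0.0175 |
| 5 | 0.0175 | 0.2364 | 0.0041 | 0.4915 | 0.0086 |
| 6 | 0.0039 | 0.4629 | 0.0018 | 0.7121 | 0.0028 |
| 7 or more | 0.0008 | – | 0.0006 | – | 0.0007 |
| Sum | | | 0.0203 | | 0.0698 |

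Across the permitted range, with r = 9:

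| n | Type I error | Power at 30% |
|---|---|---|
| 42 | 2.0% | 91.1% |
| 45 | 3.0% | 94.1% |
| 48 | 4.3% | 95.9% |
| 50 | 5.3% | 96.6% |
| 53 | 7.0% | 97.3% |

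At the cap, type I error is 6.98 / 2.03 = 3.4 times the value at 42. Power rises, so only the false-positive side is harmed.

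**Step 3. How large is the galactose arm likely to be?** Subgroup Analysis says: "It is anticipated that approximately 80% of the enrolled patients" will have P_alb above 0.5. Then 42 / 0.80 = 52.5, which agrees with the cap of 53. As an illustration, assume that enrolment stops at the 42nd galactose patient with P_alb above 0.5, capped at 53, with patients independent. The mean arm size is 51.3, and the arm reaches 53 in about 47% of such trials. It stays at 42 with probability below 0.01%. The average type I error with r = 9 is 6.0%.

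**Step 4. Thresholds that fit the size.**

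| n | Threshold | Type I error | Power at 30% |
|---|---|---|---|
| 42 | 9 | 2.03% | 91.1% |
| 43 | 10 | 0.85% | 86.6% |
| 44 | 10 | 1.00% | 88.3% |
| 45 | 10 | 1.16% | 89.8% |
| 46 | 10 | 1.35% | 91.1% |
| 49 | 10 | 2.03% | 94.0% |
| 50 | 11 | 0.90% | 91.1% |
| 53 | 11 | 1.37% | 93.9% |

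At 53 patients a threshold of 10 would give 3.3%, so 11 is the smallest count that keeps type I error at or below the 42-patient value.

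**The case against.** The strongest reply is that the rule is written with its denominator, 42 patients. The article never states a rule of 9 out of 53, and at 42 the 2% is right. This stands. The 7.0% is conditional on carrying the count of 9 to the whole enlarged arm. A reader might infer that the plan's error calculation is wrong, or that galactose's false-positive rate simply is 7.0%. The documents support neither. If the rule used the first 42 galactose patients, the rate would stay at 2.0%, and it would be near that for 42 patients with P_alb above 0.5. However, the article names neither set. It assesses the primary outcome in all randomised patients and calls the P_alb analysis secondary. On any reading the rule for an arm of 43 to 53 is unstated.

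A second reply is that a statistical analysis plan, not shown here, may adapt the cut-off to attained size. It may. But the article itself puts the threshold, the enlarged arm and a 2% claim for each treatment group side by side, and they do not fit together.

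A reader might also infer that the extra galactose patients would enter after the other arms had filled, and so would not be concurrent with their comparators. The article gives neither the allocation scheme nor the time at which P_alb results become available. A larger galactose allocation planned from the start would leave them concurrent. That inference is not supported and forms no part of this point.

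Finally, this is a Phase II screen, only one arm is affected, and power does not suffer. That limits the severity but does not remove the inconsistency.

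**Conclusion.** The point holds as an incomplete decision rule. The threshold and the 2% are correct for 42 patients and are asserted for every group, yet one arm may reach 53 and has no threshold of its own. Applied unchanged to all galactose patients, the count of 9 gives a type I error between 2.0% and 7.0% depending on final size. The average is about 6.0% under the plan's 80% share and the stopping assumption in Step 3. These figures rest on a 10% null rate, independent responses and the stage 1 rule as written. Adalimumab is unaffected. This should be fixed, but it does not undermine the design.

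**What to change.** Before outcomes are known, state the galactose threshold by attained arm size: at least 9 responders at 42 patients, at least 10 at 43–49, and at least 11 at 50–53. Type I error then stays at or below 2.03%, with power from 86.6% to 93.9%. The cost is a sentence or two and no extra patients. Power falls below the stated 90% at 43 to 45 patients. Under the Step 3 assumptions the arm ends at one of those sizes in about 1.3% of trials (0.07% + 0.31% + 0.90%).

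Alternatively, state that the activity decision alone uses the first 42 randomised galactose patients. This keeps the rule and its 2% as written, but leaves up to 53 − 42 = 11 randomised patients out of that decision.

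Under either option, keep all randomised patients in the ranking. Ranking Selection Component compares response rates, which does not require equal arm sizes.
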